## Metabolomics Research

### Establishment of TD-related Metabonomics Database

We conducted a comprehensive search across several databases and documents, including HMDB, Medline, NCBI, Web of Science, Wanfang Database, China Journal Network, and etc., to investigate the metabolic process and potential metabolites associated with this disease. This findings serve as a valuable reference for sample processing, detection, and analysis.

### Sample collection and processing

#### Sample collection

##### Urine sample

Prior to sample collection, it is essential to wash your hands thoroughly. Collect a urine sample larger than 1 mL and store it at a temperature of 4 °C. Allow the sample to stand for a period of time. Following this, centrifuge 1 mL of the urine at a temperature of 4 °C, with the settings at 10,000 rpm for 5 min. Absorb 100 µL of the supernatant and transfer it into appropriately numbered EP tubes. Repeat this process, subpackaging the sample into multiple tubes to prevent repeated freezing and thawing. Finally, rapidly freeze the tubes in liquid nitrogen and store them in a refrigerator at -80 °C.

##### Fecal sample

To begin, prepare the feces container, wash your hands thoroughly, and wear gloves. Use sterile spoons, provided with the sampling tube cover, to collect 2–3 spoons of fecal samples for each tube. Once collected, immediately place the samples in low-temperature conditions such as liquid nitrogen, dry ice, ice bags, or a refrigerator set at 4 degrees Celsius. Subsequently, promptly transfer the samples to a -80-degree refrigerator for long-term storage.

#### Sample pretreatment

Urine: Thaw the stored urine at 4℃, shake and mix well, take 500µL and transfer it to a 1.5 mL EP tube, centrifuge at 12,000 rpm for 10 min at 4℃ to remove sediment, take 200µL of the supernatant and transfer it to another 1.5 mL EP tube, add 200µL of methanol, vortex for 3 min, centrifuge at 12,000 rpm for 10 min at 4℃, collect the supernatant for analysis.

Fecal: Add the sample and n-hexanoic acid to sterile distilled water, mix well, then add 0.4 ml of sulfuric acid (approximately 50% mass fraction) and 2 ml of anhydrous ether. Place the mixture on a shaker and mix for 30 min, followed by centrifugation at 3000r/min. Add anhydrous CaCl2 to remove residual moisture, and transfer the supernatant for GC determination.

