### Metabonomics analysis

#### Sample analysis

In this experiment, the ESI-MS method combining positive and negative ion detection modes will be used to treat urine and feces accordingly using the above pre-treatment methods, and the liquid chromatography conditions and mass spectrometry (MS) detection parameters will be optimized with a scanning range of m/z50-1000 to maximize the coverage of the metabolite groups. The goal is to establish an RP/HILIC-UPLC-TOFMS technique for analyzing various metabolites in urine and feces samples. 20 µL and 1 g of all test samples will be absorbed and thoroughly mixed in the entire analysis batch to be quality control (QC) samples.

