#### Multivariate Statistical Analysis

Preprocessed data will be subjected to unsupervised data analysis using Principal Component Analysis (PCA). A score plot will be used to observe clustering of data from different groups and to remove outlier samples. A loading plot will be utilized to identify components that contribute to inter-group variability, with special attention given to excluding prototype compounds and their metabolites. Additionally, univariate analysis such as fold change (FC) and t-tests will be performed to identify components that exhibit significant statistical differences. Pattern recognition methods, such as Partial Least Squares Discriminant Analysis (PLS-DA) and Orthogonal Partial Least Squares Discriminant Analysis (OPLS-DA), will be employed, and targeted programming and execution using languages such as R or C will be based on the characteristics of the analysis data. Integration of HILIC-TOFMS and RPLC-TOFMS data will be conducted to identify differential components. Multiple methods, including t-tests (*p* < 0.05), FC analysis (FC > 2), and PLS-DA (VIP > 1.5), will be used to screen and confirm potential biomarkers that contribute to inter-group differences, thus identifying potential biomarkers associated with acupuncture treatment in children with TD.

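### Fecal samples are prepared for GC, but the only analysis described for them is LC-ESI-TOFMS; the two must be reconciled before stored feces are extracted

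*Protocol article*

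**What the plan says.** Three consecutive parts of the Metabolomics Research section bear on this.

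- **Sample pretreatment.** Feces are mixed with n-hexanoic acid in sterile water. The text continues "then add 0.4 ml of sulfuric acid (approximately 50% mass fraction) and 2 ml of anhydrous ether". After shaking, centrifugation and drying over CaCl2, it ends with the instruction to "transfer the supernatant for GC determination".
- **Sample analysis.** Electrospray mass spectrometry in both ion modes "will be used to treat urine and feces accordingly using the above pre-treatment methods". Liquid chromatography conditions are to be optimised over m/z 50-1000 to widen coverage, and "The goal is to establish an RP/HILIC-UPLC-TOFMS technique for analyzing various metabolites in urine and feces samples".
- **Multivariate Statistical Analysis.** "Integration of HILIC-TOFMS and RPLC-TOFMS data will be conducted to identify differential components". Candidate markers are screened by t-test (p < 0.05), fold change (> 2) and PLS-DA (VIP > 1.5).

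The Introduction also names LC-MS as the technique for urine and feces and announces a wide screen of both. Identification of potential biomarkers relies on information from TOFMS. The Abstract and Table 1 list urinary and fecal metabolomics as a secondary outcome.

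**The concern.** The article gives a specific recipe for preparing feces and a specific platform for analysing them, and the two name different techniques. GC is read here as gas chromatography; the article does not expand the abbreviation. Sample analysis does not merely leave the preparation open. It points back to the pretreatment just described and applies it to the LC run.

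At stake is what the fecal data set will be. The PCA, PLS-DA and OPLS-DA models, the three-way marker screen and the KEGG pathway step all presuppose an untargeted LC-TOFMS feature table. If the laboratory follows the pretreatment text, it holds a GC extract for which no analysis is planned. If it follows the analysis text, it must use a preparation that the article does not describe. Whoever extracts the samples will have to choose, and the article gives no basis for the choice.

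**Working it through.** The article states no figure to reproduce. The check is a comparison of the text, a count, and a test of whether the problem reaches urine.

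**1. The two matrices side by side**

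| Step | Urine | Feces |
|---|---|---|
| Preparation (Sample pretreatment) | Thaw, spin, add methanol, spin, supernatant for analysis | Acid and ether extraction, dry over CaCl2, supernatant for GC |
| Platform (Sample analysis) | RP/HILIC-UPLC-TOFMS, ESI | RP/HILIC-UPLC-TOFMS, ESI |
| Data combined (Multivariate Statistical Analysis) | HILIC-TOFMS and RPLC-TOFMS | HILIC-TOFMS and RPLC-TOFMS |
| GC conditions or GC data handling | Not needed | None described |

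The urine column is consistent from top to bottom. The fecal column changes technique between its first and second rows, and no step joins them.

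**2. Samples concerned**

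Inputs: 60 children with TD, sampled at baseline and at the end of treatment, and 30 healthy children sampled at baseline only (Abstract, Methods). One fecal sample per child and time point is assumed.

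- Full retention: 60 x 2 + 30 x 1 = 150.
- With the 20% dropout from Sample size, assumed to remove week 12 samples only: 60 + 60 x 0.8 + 30 = 60 + 48 + 30 = 138.

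**3. Does the problem extend to urine?**

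Inputs: 1 mL is spun and the supernatant divided into 100 µL tubes (Urine sample); 500 µL is drawn at pretreatment (Sample pretreatment).

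- Tubes needed: 500 / 100 = 5.
- Tubes available at most: 1000 / 100 = 10.
- With an assumed supernatant loss of 10%, 20%, 30% or 50%: 9, 8, 7 or 5 tubes.

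Five tubes remain across this range, so pooling supplies the 500 µL. The article does not mention pooling, but the urine assay can be carried out.

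**The case against.** The strongest reply is one of scope. Metabolomics is a secondary, marker-screening outcome. Sample analysis says that LC conditions are still to be optimised, so the LC procedure is not presented as final. The article also condenses a fuller protocol, and laboratory detail may sit there. The point about scope stands and limits the weight of the finding. The rest does not remove it: optimising LC conditions does not turn a GC preparation into an LC one, and the difficulty is two stated procedures that disagree, not detail left out.

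Four stronger readings are tempting, and the documents do not support them.

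- **That the whole metabolomics outcome cannot be produced.** A reader might infer this from the 100 µL tubes set against the 500 µL draw. But the Urine sample section says "Repeat this process, subpackaging the sample into multiple tubes to prevent repeated freezing and thawing", and five pooled tubes are enough. Nor is a larger aliquot clearly better: tubes of 520 µL (500 plus 20 for quality control) would give 1000 / 520 = 1.9, so one full tube per spin, against the stated purpose of having several.
- **That fecal storage biases the comparison of groups.** The Fecal sample section tells staff to "immediately place the samples in low-temperature conditions such as liquid nitrogen, dry ice, ice bags, or a refrigerator set at 4 degrees Celsius" and then to move samples promptly to -80 degrees. The range is wide, but the same instruction covers every child. Nothing ties storage to group, and a single condition with a time limit is detail that an article commonly leaves to a laboratory manual.
- **That the ether extract would miss the compounds that motivate the study.** The documents do not say what this extract recovers. The Introduction draws its neurotransmitter evidence largely from urine and cerebrospinal fluid and its amino acid evidence from urine and serum, while its case for feces rests on the gut flora.
- **That 150 samples are lost.** That number is a ceiling before dropout, and samples not yet extracted are not lost.

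**Conclusion.** The contradiction is real and confined to feces. The fecal part of a named secondary outcome, at most 150 samples and 138 under the dropout assumption above, has a preparation that does not match its stated analysis. The conclusion rests on the wording of the three sections alone and needs no assumption about extraction chemistry beyond reading GC as gas chromatography. It should be corrected, but it does not threaten the trial's main result.

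**What to change.** Reconcile Sample pretreatment with Sample analysis and Multivariate Statistical Analysis before any more stored feces are extracted, in one of two ways.

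1. Replace the fecal paragraph under Sample pretreatment with an extraction compatible with the RP/HILIC-UPLC-TOFMS run.
2. If the ether/GC procedure is wanted, list it as a separate targeted assay on its own aliquot, with its instrument, the compounds measured and its own analysis. If feces also stay in the untargeted LC run, that run still needs its own stated preparation. If they do not, remove feces from the LC sections and state that the fecal outcome is targeted.

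The cost is laboratory wording, with no new visits and no change to sample size. The Fecal sample section freezes feces before any extraction, so material still stored raw can follow the reconciled procedure. Recruitment is under way (Trial status), so the team should first establish whether any feces have already been extracted. Those samples may not be recoverable and should be reported separately.

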### Metabonomics analysis

#### Sample analysis

In this experiment, the ESI-MS method combining positive and negative ion detection modes will be used to treat urine and feces accordingly using the above pre-treatment methods, and the liquid chromatography conditions and mass spectrometry (MS) detection parameters will be optimized with a scanning range of m/z50-1000 to maximize the coverage of the metabolite groups. The goal is to establish an RP/HILIC-UPLC-TOFMS technique for analyzing various metabolites in urine and feces samples. 20 µL and 1 g of all test samples will be absorbed and thoroughly mixed in the entire analysis batch to be quality control (QC) samples.

#### Data preprocessing

The original atlas data obtained from the analysis system underwent preprocessing, followed by multivariate statistical analysis using MarkerView™ software. The primary processing steps involved setting appropriate parameters for retention time, noise threshold, minimum chromatographic peak width, and allowable error of molecular weight to perform background subtraction, chromatographic peak search, and calibration on the raw chromatographic data. The “80% rule” is applied to eliminate missing values. Additionally, if necessary, the analysis data could be normalized using the “always available mass spectrometry signal method” and “osmotic pressure normalization method”.

#### Multivariate Statistical Analysis

Preprocessed data will be subjected to unsupervised data analysis using Principal Component Analysis (PCA). A score plot will be used to observe clustering of data from different groups and to remove outlier samples. A loading plot will be utilized to identify components that contribute to inter-group variability, with special attention given to excluding prototype compounds and their metabolites. Additionally, univariate analysis such as fold change (FC) and t-tests will be performed to identify components that exhibit significant statistical differences. Pattern recognition methods, such as Partial Least Squares Discriminant Analysis (PLS-DA) and Orthogonal Partial Least Squares Discriminant Analysis (OPLS-DA), will be employed, and targeted programming and execution using languages such as R or C will be based on the characteristics of the analysis data. Integration of HILIC-TOFMS and RPLC-TOFMS data will be conducted to identify differential components. Multiple methods, including t-tests (*p* < 0.05), FC analysis (FC > 2), and PLS-DA (VIP > 1.5), will be used to screen and confirm potential biomarkers that contribute to inter-group differences, thus identifying potential biomarkers associated with acupuncture treatment in children with TD.

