## Materials and methods

### Study design and participants

This is a randomized controlled trial, recruiting a total of 90 children (30 healthy children and 60 children with TD) in the outpatient department of acupuncture and rehabilitation department of Affiliated Hospital of Nanjing University of Traditional Chinese Medicine, in which they will be divided into non-intervention group and intervention group. The non-intervention group consists of 30 healthy children while the intervention group consists of 60 children with TD. The intervention group will be randomly allocated into either the treatment group or the control group, with 30 children randomly assigned in each group. Participants with tic disorder will also be recruited through posters and official WeChat accounts. The researchers will use the American Psychiatric Association DSM-5 criteria for tic disorder to assign a diagnosis. Individuals who meet the inclusion criteria will receive free complimentary clinical testing and some treatment subsidies to encourage enrollment. The details of the clinical trial and the collection of samples will be explained to the parents of the patients before obtaining their written consent. This research was approved by the Ethics Committee of the Affiliated Hospital of Nanjing University of Traditional Chinese Medicine (Jiangsu Provincial Hospital of Traditional Chinese Medicine) (2023NL-095-02), and the trial has been registered in China Clinical Trial Registration Center(ChiCTR2300075188).The flow of the trial is presented in Fig. 4. The schedule of the trial is shown in Table 1.

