### Randomization

The subjects will be randomly assigned to two groups: the experimental group and the control group. There will be 30 cases in each group. Randomization was performed using the R software, generating a random number table with a block length of 4 and a distribution ratio of 1:1. Upon enrollment of eligible subjects, the randomizer allocated them to groups based on the order of their entry into the trial, labeling “1” as the experimental group and “2” as the control group. Throughout the trial, the acupuncturist will be aware of the patient’s group allocation. The subjects, evaluators of therapeutic effects, and individuals conducting the statistical analysts will be blinded to group allocation.

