## Statistical analysis

Descriptive statistical analysis, qualitative indicators are described by frequency table, percentage or composition ratio; Quantitative indicators are described by mean, standard deviation, or median, lower quartile (Q1), upper quartile (Q3), minimum value and maximum value.

The qualitative data are analyzed using the chi-square test, Fisher’s exact probability method, Wilcoxon rank sum test, CMH χ2 test, and WLS covariance. For the quantitative data, the normal distribution is verified using the t test (homogeneity test of variance is conducted between groups, with a test level of 0.05, and the Satterthwaite method is used for correction when the variance is uneven). For non-normal distribution, the Wilcoxon rank sum test and Wilcoxon signed rank sum test are employed, along with GLM covariance. A two-sided test is uniformly used for the hypothesis testing, and test statistics along with their corresponding P-values are provided, with *P* ≤ 0.05 indicating statistical significance and *P* ≤ 0.01 indicating high statistical significance.

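### Outlier samples are removed from a PCA score plot that also displays the groups, with no limit and no condition that labels are hidden, so removal guided by group position is permitted before the metabolomics screen

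*Protocol article*

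**What the plan says.** Multivariate Statistical Analysis in the Protocol article opens with the decomposition: "Preprocessed data will be subjected to unsupervised data analysis using Principal Component Analysis (PCA"). The next sentence gives the score plot its two uses: "A score plot will be used to observe clustering of data from different groups and to remove outlier samples". Fold change, t-tests, PLS-DA and OPLS-DA follow. The screening thresholds are "t-tests (*p* < 0.05), FC analysis (FC > 2), and PLS-DA (VIP > 1.5"), and these methods "will be used to screen and confirm potential biomarkers that contribute to inter-group differences".

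The section gives no numerical definition of an outlier, no condition that removal is decided without group labels, and no repeat analysis with all samples kept. Sample analysis describes pooled material, "thoroughly mixed in the entire analysis batch to be quality control (QC) samples", but the removal step makes no reference to it. Randomization states that those doing the statistical analysis are blinded to allocation.

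**The concern.** A sample that lies apart on a score plot may be an analytical failure, a child whose metabolism truly differs, or a strong responder. The plot alone cannot tell these apart. If the person deciding can also see which group each point belongs to, the decision can depend on group position even though the decomposition ignored the labels.

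Removal of that kind acts before any test. Dropping points far from their own group's centre shrinks the within-group spread; dropping points that lie towards the other group moves the means apart. Either raises the chance of a spurious biomarker, and a later multiplicity correction cannot repair data already selected by group.

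What is at stake is a named secondary outcome. The screen feeds the correlation with scale scores and the KEGG pathways under Metabolic pathway analysis, on which the account of mechanism rests.

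**Working it through.** **Plan figure.** The plan gives no error rate for this screen, so there is none to reproduce. Its group size is the one figure used below.

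**Inputs from the Protocol article**
- Group size: "with 30 children randomly assigned in each group" (Study design and participants), allocated "with a block length of 4 and a distribution ratio of 1:1" (Randomization).
- Sidedness: "A two-sided test is uniformly used for the hypothesis testing" (Statistical analysis).
- Threshold: p < 0.05 per metabolite (Multivariate Statistical Analysis).

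**Assumptions, not in the documents**
- 200 metabolites, with five latent factors carrying 30% or 60% of the variance; no true group difference.
- Full enrolment of 30 against 30.
- k = 1, 2 or 3 samples removed per group, chosen on the first two principal components. Two of 30 is 2/30 = 6.7% of a group.

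**Test.** After removal each group has n = 30 − k, and t = (mean₁ − mean₂) / (s_pooled × √(2/n)), two-sided at 0.05. There were 1,000 runs per cell. Ranges span the two variance assumptions; the label-blind row also spans the three numbers removed.

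| Removal rule | Removed | Test on PC1 score | Per-metabolite test |
|---|---|---|---|
| None | 0 | 4.3–4.4% | 4.9–5.0% |
| Label-blind, distance from pooled centre | 2, 4 or 6 in all | 4.7–6.7% | 4.7–5.1% |
| Furthest from own group's centre | 1 per group | 7.0–7.6% | 5.4–5.6% |
| | 2 per group | 10.0–10.3% | 5.6–6.0% |
| | 3 per group | 11.4–12.5% | 5.7–6.5% |
| Furthest towards the other group (worst case) | 1 per group | 14.9–16.3% | 6.2–7.9% |
| | 2 per group | 32.4–35.3% | 8.1–11.1% |
| | 3 per group | 44.5–47.5% | 9.8–14.3% |

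The Monte Carlo standard error of a PC1 rate near 5% is √(0.05 × 0.95 / 1000) = 0.7 percentage points. Five of the six label-blind PC1 cells lie between 4.7% and 5.5%; the sixth is 6.7%.

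**Scale.** With the assumed 200 metabolites, the t-test alone gives 200 × 0.05 = 10 false signals on average. At 6.5% it gives 13, and at 14.3% about 29.

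**Single-axis bound.** A simpler simulation removes samples on one normal variable and then tests that same variable (20,000 trials). With k = 0, 1, 2, 3 the rates are:
- furthest towards the other group: 4.7%, 18%, 41%, 72%;
- furthest from own centre: 4.8%, 9%, 13%, 16%;
- label-blind removal: 4.4–4.7%.

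This bounds the effect for a metabolite that nearly coincides with the score axis.

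**Adding the fold-change filter.** This is the single-axis case with log-normal values, k = 2, requiring both p < 0.05 and FC > 2. For assumed log-SDs of 0.5, 0.8, 1.0 and 1.3:
- own-centre removal: 0%, 0.5%, 2.6%, 6.5%;
- worst-case removal: 0%, 4.7%, 17%, 31%, against 41% with the t-test alone.

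**The case against.** The strongest reply is that the text does not say a sample is removed because it sits away from its group. A reader might infer that children who do not fit will be dropped and that separation will appear where none exists. The documents do not support that. The PCA is called unsupervised, and removing points far from all the data is an ordinary reading; under it the error rate stays near 5%. This part stands: the harm is something the wording permits, not something it prescribes.

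Second, outlier limits and sensitivity analyses are often left to an analysis plan or laboratory procedure, and neither is shown. The absence of a limit alone would therefore not be a finding. The point survives because the article states the rule itself, and that rule gives the plot on which groups are compared the further job of choosing deletions.

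Third, analysts are blinded to allocation. This lowers the risk but does not close it. Coded labels are enough to show which point lies away from its own cluster. The comparison of healthy children with children with TD is not an allocation, and the blinding statement does not say it is masked.

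Fourth, a reader might take 18–72% as the false-biomarker rate. It is not. It requires deleting exactly the points lying furthest towards the other group, on one axis that is then tested. Such points lie in the overlap between groups, usually not where score-plot outliers are found. The fold-change and VIP filters also apply and lower the absolute rates. They are computed on the same reduced data, however, so they do not undo the selection.

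**Conclusion.** The point holds as a weakness in a stated rule. Samples may be removed by eye from a plot showing the groups, ahead of the group tests, with nothing to prevent group position from guiding the choice.

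If it does guide the choice, the per-metabolite error of a nominal 5% t-test becomes about 5.4–6.5% for own-centre removal and about 6–14% in the worst case. On a single score axis the worst case is 18–72%. If labels are ignored, the error stays near 5%, so the fault lies in the use of group position and not in outlier removal as such.

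The figures rest on 30 against 30, one to three removals per group, and an assumed number and correlation of metabolites. They are t-test rates before the fold-change and VIP filters, not final biomarker error rates. Only the secondary metabolomics screen and what is built on it are affected; YGTSS is not. This is a cheap improvement worth making, not a threat to the trial's main comparison.

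**What to change.** Reword the removal step in Multivariate Statistical Analysis as follows:
- Decide exclusions before any group or visit label, coded or not, is attached to the samples.
- Use a prespecified numerical limit applied to all samples pooled, for example a Hotelling T² limit, and/or documented technical failure judged against the existing pooled QC samples. Restricting removal to technical failure alone is not necessary, since a label-blind limit already keeps the error near 5%.
- Report the number of samples removed by group.
- Repeat the biomarker screen with all samples kept and show both results.

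The cost is a change of wording and one further run of the screen; no new samples or children are needed. The downside is slightly more analysis work, and some extreme samples stay in, so the plots will look less clean.
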